**Fig. 1 Fig1:**
[figure not shown]
Flow diagram of the GReat-Child trial design

The standard deviation (SD) of the BMI-for-age z-score obtained from a previous study (Madsen et al. 2009) is taken into consideration for the sample size calculation of this present trial. With the SD of the BMI z-score equal to 0.10, giving a detectable difference of 0.08, a sample size of around 25 children per group at 12 weeks would give 80 % power at the 0.05 significance level. The sample size was estimated using the following equation (Naing 2009):$$ {\rm n} =[2 \upsigma^2/\Updelta^2]  ({\rm Z}_{\upalpha}+{\rm Z}_{\upbeta})$$where n = estimated sample size, σ = standard deviation for BMI-score from previous study = 0.10, ∆ = detectable difference = 0.08, Z_α_ = significance level for two-sided test = 1.96, Z_β_ = 80 % power of study = 0.84.

The sample size required for this study is 25 per group. While taking into account a non-response rate of 50 %, the required sample size for each group is increased to 38; therefore, the total number of children needed is 76. Any children who wish to dropout are allowed to do so, with the reasons being noted and analysed.

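### The 50 % non-response allowance gives 38 per group where 50 are needed; at that loss 19 remain and power is about 67 %, not 80 %

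*Protocol article*

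**What the plan says.** All of this stands in the protocol article, Methods, under the heading on trial design and sample size calculation, in the text after Fig. 1.

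- The planning values are given as "With the SD of the BMI z-score equal to 0.10, giving a detectable difference of 0.08", with "significance level for two-sided test = 1.96" and "80 % power of study = 0.84".
- From these the article concludes that "a sample size of around 25 children per group at 12 weeks would give 80 % power at the 0.05 significance level", and repeats: "The sample size required for this study is 25 per group".
- It then takes 50 % non-response into account and states that "the required sample size for each group is increased to 38; therefore, the total number of children needed is 76". It neither shows the step from 25 to 38 nor defines non-response. The next sentence deals with children who drop out.
- The equation is printed as 2σ²/Δ² multiplied by the sum of the two Z values, with no exponent on that sum.

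**The concern.** The 25 per group is a number of children with data at 12 weeks. An allowance for non-response should give a starting number that still yields 25 after the stated proportion is lost, so the base size is divided by the proportion retained. The stated 38 looks instead like the base size multiplied by one plus the loss rate. The two calculations nearly agree when the loss is small and diverge widely at 50 %.

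At stake is the power claim for the primary outcome. If the loss that the plan allows for occurs, fewer children than required are analysed, and a null result would be read against a power that the trial did not have. The equation in the same passage does not yield the 25 used either, so a reader cannot reproduce the calculation as printed.

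**Working it through.** **Inputs, all from the sample-size text:** σ = 0.10; Δ = 0.08; Zα = 1.96 (two-sided 0.05); Zβ = 0.84 (80 % power); two equal groups; non-response 50 %.

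**1. Base size.** The plan's figure is reproduced with the usual squared form:

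- 2σ²/Δ² = 2 x 0.01 / 0.0064 = 3.125
- (1.96 + 0.84)² = 2.80² = 7.84
- n = 3.125 x 7.84 = 24.5, rounded up to 25

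The equation as printed, without the square, gives 3.125 x 2.80 = 8.75. The 25 therefore comes from the squared form, and the missing exponent does not carry into later figures.

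**2. Allowance for 50 % non-response.**

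- Dividing by the proportion retained: 25 / (1 - 0.5) = 50 per group, 100 in total.
- Multiplying by one plus the rate: 25 x 1.5 = 37.5, rounded up to 38 per group, 76 in total.

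The second line reproduces the stated figures exactly. That it was the step taken is an inference, because the article does not print it.

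**3. What 38 per group leaves.**

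- At 50 % loss: 38 x 0.5 = 19 per group, 6 fewer than the 25 required.
- Largest loss that still leaves 25: 1 - 25/38 = 0.342, or about 34 %.
- At 40 % loss: 38 x 0.6 = 22.8 per group, with power 77 % by the normal formula.

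**4. Power at the plan's own SD and difference.** The normal formula is Φ(Δ / (σ√(2/n)) - 1.96). For n = 19 this is Φ(0.8 x √9.5 - 1.96) = Φ(0.506). The t-test column uses the noncentral t distribution with a standardised difference of 0.08/0.10 = 0.8.

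| Analysed per group | Normal formula | t test |
|---|---|---|
| 19 | 69.4 % | 67.0 % |
| 25 | 80.7 % | 79.1 % |
| 38 | 93.7 % | 93.1 % |
| 50 | 97.9 % | 97.7 % |

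Compared on one basis, the fall from 25 to 19 is about 11 points by the normal formula (80.7 to 69.4) and about 12 by the t test (79.1 to 67.0).

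**5. Difference detectable with 80 % power at 19 per group.** By the normal formula, 2.80 x 0.10 x √(2/19) = 0.091, against the planned 0.08.

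**The case against.** The strongest reply is that non-response is undefined and may mean refusal at invitation rather than loss after enrolment, since dropout has its own sentence. If 38 children per group are enrolled and all are measured, power is about 93 % and there is no shortfall. The phrase may also be loose wording for recruiting half as many again, in which case the wording is at fault and not the number. In addition, entry requires a parent willing to attend counselling, a criterion meant to select families who will complete the programme, so a loss of 50 % may be unlikely.

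Part of this stands. The power loss is conditional: it occurs only if loss from the 38 exceeds about 34 %, and it is not a forecast. The mismatch, however, survives every reading. If half refuse at invitation, 50 must be approached to obtain 25, and approaching 38 yields 19. If 38 is the number enrolled and kept, 50 % was not the loss that produced it. If a 50 % margin was meant, it covers a loss of about one third, and the text calls it a rate of non-response.

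Two further points are fair. The power figures assume an unadjusted comparison of independent children, whereas the article assigns one school to each condition and plans a baseline-adjusted repeated-measures ANCOVA. They are therefore figures under the plan's own sample-size formula, not the power of the final analysis. The missing square is a separate printing error that changes no downstream number and adds nothing to the severity of the main point.

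**Conclusion.** The concern holds. A requirement of 25 per group with 50 % non-response means 50 per group (100 in total), not 38 (76 in total): a shortfall of 12 per group, 24 in total. If the stated loss occurs among the 38, 19 per group are analysed and power is 67 % by t test (69 % by the plan's normal formula) instead of 80 %. The chance of missing the effect that the trial was sized for is then about one in three rather than one in five. The 38 protects the required 25 only up to a loss of about 34 %.

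These results take the article's SD, difference, significance level and independence of children at face value. The base figure of 25 is sound on those terms; only the inflated figures and the printed equation are wrong. Because the figure supports the power claim for the primary outcome, it must be corrected.

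**What to change.** Make the sample-size text agree with its own inputs in one of two ways.

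- **If 38 per group is kept:** replace the non-response sentence with wording such as: *38 per group retains 25 per group if loss is at most 34 %; at 50 % loss 19 per group remain and, under the SD, difference and independence assumed here, power is about 67 % (t test).*
- **If 50 % loss is truly expected and 80 % power is to be claimed:** state the requirement as 50 per group, 100 in total.

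In either case, say whether non-response means refusal before enrolment or loss before the 12-week measurement, and print the equation with the sum of Zα and Zβ squared, so that it gives 24.5 and hence 25.

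The first option costs two sentences and one exponent. It needs no further recruitment and no change to the analysis, but the stated power becomes less favourable. The second raises the stated requirement by 24 children.

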### Rationale for the GReat-Child Trial

The GReat-Child trial is developed based on social cognitive theory (SCT). The SCT provides a theoretical foundation for identifying modifiable behaviours, as well as to structure behaviour-change interventions. Additionally, the SCT explains human behaviour in terms of a reciprocal relationship, the triadic and dynamic relationships in which behaviour patterns, personal characteristics and environmental influences interact (Baranowski et al. 2002). This theory has provided the conceptual framework for several multi-component interventions involving children and parents, which have resulted in positive dietary behaviour change (Baranowski et al. 2002).

The social cognitive theory concepts and applications for the present trial are shown in Table 1. Several SCT techniques will be applied in the present trial in order to assist the parents and children in raising their awareness of whole grain consumption and a healthy balanced diet, as well as to motivate the children and parents to make changes in order to manage childhood obesity. The theory constructs addressed in the GReat-Child trial include behaviour factors such as the behavioural capability (whole grain and healthy eating knowledge, as well as behavioural skills) and usual food choice (choice between pairs of foods); personal factors such as self-regulation (goal-setting), self-efficacy (confidence to carry out behaviours successfully) and outcome expectancies (preferences); as well as environmental factors consisting of the availability and accessibility of wholegrain foods and a healthy balanced diet (Burgess-Champouxt et al. 2007). The present trial is adapted from a combination of interventions named “Power of 3: Get Healthy with Wholegrain Foods” (Burgess-Champouxt et al. 2007) and “WATCH clinic” (Madsen et al. 2009).

**Table 1 Tab1:** Social cognitive theory (SCT) concepts and application for GReat-Child trial

SCT constructs	Application	Learning activities
Behavioural domain		
Behavioural capability	Provided whole grain and healthy eating knowledge	Participation in whole-grain and healthy balanced diet quiz in six 30-min nutrition education classes Children were required to draw the healthy plate model on the blackboard Using food labels to identify foods as whole grain or refined grains Locating grain food group and grain food items on the Food Guide Pyramid Individual diet counselling for the parents to identify the whole-grain foods, as well as the advantages of whole grain consumption
Food choice	Served a variety of whole-grain foods on a daily basis	Tasting whole-grain foods for taste, appearance, texture and acceptance Researcher introducing variety of whole-grain food during school delivery and let the children familiarising with it Identifying whole-grain and healthy balanced diet’s labels during individual diet counselling for the parents
Personal domain		
Self-efficacy	Provided practical experiences that emphasised tasting, selecting and preparing whole-grain foods	Whole grain recipe booklet provided to parents during individual diet counselling, to help them prepare and serve whole-grain food at home Handy tips included in the whole grain booklet during individual diet counselling, to show the parents easier way to achieve the recommendation to eat half of the grains as whole grain Learning about menu planning for balanced diet during six 30-min nutrition education and individual diet counselling Reading food and nutrition labels on the packaging of whole-grain foods, to overcome barriers in selecting and identifying the whole-grain foods
Reinforcements	Children were rewarded and received praise when they correctly answer questions on whole-grain and healthy eating diet	Participation in whole-grain and healthy balanced diet quiz during nutrition education classes
Environmental domain		
Observational learning	Served a variety of whole-grain foods on a daily basis	Children observed how to prepare a convenient whole-grain breakfast Whole-grain food recipes provided to parents
Availability	Provided information to encourage the parents to increase availability of whole-grain foods and healthy diet at home	Individual diet counselling and booklet provided to advocate for consumption of more whole-grain foods, as well as balanced diet at home

## GReat-Child Trial Components

### Overview

An overview of the GReat-Child trial is shown in Table 2. This trial consists of three components addressing the behaviour, personal and environmental factors based on the SCT: (1) a family involvement component; (2) six 30-min nutrition education classes and (3) the school delivery of whole-grain foods. A quasi-experimental study design is utilized to increase the awareness and consumption of whole grain, modify the availability of whole-grain food by providing selected wholegrain foods every school day during break time, as well as to manage childhood obesity by reducing anthropometric measurements. Children from the intervention group received a 12-week intervention programme with another 6-month follow up. In contrast, the children in the control group do not receive any intervention activities, however, for ethical purposes, a health talk is conducted after the entire GReat-Child Trial is completed.

**Table 2 Tab2:** The overview of GReat-Child trial

Components	Contents
Classroom nutrition education	Six 30-min nutrition education classes On fortnightly basis Employed simplified “Food Guide Pyramid” and “visual plate model” Module included: An overall food pyramid education Energy balance education A visual plate model An overall whole grain education Source and sampling of wholegrain foods Reading labels
Twelve-week school delivery of wholegrain foods	Provide opportunities for children to experience and accept wholegrain foods. On daily basis, during school-break time Selected wholegrain food: wholegrain bread, wholegrain ready-to-eat cereals and wholegrain biscuits
Family involvement	A session of individual diet counselling after the baseline data collection and prior to 12-week intervention Employed simplified “Food Guide Pyramid” and “visual plate model” Parents to increase the availability of wholegrain foods and balanced diet at home Encourage parental role modelling for consuming wholegrain foods and healthy diet Mother was invited to attend an in-depth interview session using a semi-structured telephone interview, at the conclusion of the GReat-Child Trial (9th month), to identify the obstacles they had encounter in increasing the wholegrain consumption

### Family involvement

This component includes a session of individual diet counselling with the parents prior to the 12-week intervention, just after the baseline data collection, which is based on the concept of the SCT (Table 1). Each parent is seen individually by a dietitian, and the dietary strategies used are the simplified “Food Guide Pyramid” and “visual plate model”. During the session, the parents is informed individually about their child’s BMI z-scores, percentage of body fat and waist circumferences, which are obtained from the baseline data collection. A dietary meal plan is given, based on modification of individual dietary recalls, which are also obtained from the baseline data collection. These are done to increase the parental awareness of childhood obesity, as well as to motivate them to monitor the anthropometric measurements and dietary intakes of their children. In addition, all parents is educated on whole-grain and healthy balanced diet recommendations based on the Malaysian Dietary Guidelines for Children and Adolescents (National Coordinating Committee on Food and Nutrition Ministry of Health Malaysia. Malaysian Dietary Guidelines for children and adolescents 2013). They are taught to read food labels, identify whole-grain foods, reduce portion size and increase physical activity. Additionally, the parents are encouraged to prepare wholegrain foods with a healthy balanced diet at home. Several handy tips are given to inform the parents of easier ways to achieve the guidelines of eating half of their grains as whole grains. The aims of this component are to: (1) increase the availability of whole-grain food at home; (2) encourage parental role modelling for consuming whole-grain foods and (3) promote a dialogue between the parents and the dietitian regarding the inclusion of whole-grain foods within the context of a healthy balanced diet. In addition, each parent receives written educational materials that contain whole grain recipes, handy tips for preparing whole-grain foods and healthy balanced diet recommendations, which are discussed during the individual diet counselling session.

### Classroom nutrition education classes

Six 30-min nutrition education classes based on the SCT (Table 1) are developed and delivered to the children who enrolled in the intervention group by a dietitian. A teacher attends each of the nutrition education classes to provide disciplinary assistance when needed. The intervention group receives the nutrition education classes on Wednesday afternoon at 1 p.m., on a fortnightly basis, after finishing their regular school lessons, and before they begin their compulsory after-school co-curriculum activity, which is implemented at 1.30 p.m. based on the recommendation of the Ministry of Education. This arrangement is made so that the delivery of the nutrition education will not affect the schedule, as well as to minimize any inconvenience to all parties concerned.

The classroom nutrition education component employs a simplified “Food Guide Pyramid” and “visual plate model” in order to provide guidance on how to obtain a balanced diet, with adequate whole grain intake. The aims of this nutrition education are to (1) improve knowledge on whole grains and balanced diets; (2) reduce intake of refined carbohydrates, and substituting with high-fibre whole grain and (3) improve attitudes and practices towards whole grain by learning to identify of whole-grain foods. The nutrition education module includes: (1) energy balance; (2) food pyramid; (3) a visual plate model; (4) whole grain; (5) source and sampling of whole-grain foods and (6) understanding food labels. At the end of each nutrition education class, the children participate in a quiz session to demonstrate their acquired knowledge regarding whole grain and healthy balanced diet, and those that answer the quiz correctly are rewarded with a stationery set. Each child also receives written educational materials that contain the plate model, dietary and whole grain recommendations that are discussed in the nutrition education classes.

### School delivery of wholegrain foods

For this component, whole-grain foods are delivered on a daily basis during the school break by a dietitian. The selected whole-grain foods, such as whole-grain ready-to-eat cereals, whole-grain bread and whole-grain biscuits are supplied to the children to replace any food that the children would normally eat during break time. This arrangement is made so that 100 % of the wholegrain food distributed would be eaten by the children under the dietitian’s supervision. All food items provided are bought by the researchers and are not sponsored by any food industry. For any children who are absent on a particular day, the whole-grain foods would be distributed the next day to the absent children. The absent child would take the extra whole-grain food home for consumption later, during the weekend. To make sure the children follow the instructions given, parents are reminded via phone calls or short messages on that particular weekend.

The school delivery of the whole-grain food component focuses on the inclusion of whole-grain food examples and activities that reflect the children’s lifestyles, preferences and culture, according to the concept of the SCT (Table 1). The goals of this component are to (1) offer the equivalent of one serving of whole-grain foods to the children by replacing refined-grain foods with whole grain counterparts and (2) provide the opportunity for the children to experience and accept a healthy new repertoire of whole grain alternatives in their diet. The selected whole-grain foods are convenient and nutrient-dense foods that do not require complicated preparation.

### Intervention outcome measurements

The children are assessed on three occasions, at the baseline, at the thirteenth week and at the ninth month. All the assessments are done by one investigator throughout the study to avoid the problem of inter-interviewer variations.

### Anthropometric measurement outcomes

The primary outcome measured is the BMI-for-age z-score, which is compared between the intervention and control groups. The body weight and height of each child are measured twice, according to standard procedures, using a calibrated Tanita digital scale Model SC-330 (Tanita Co., Tokyo, Japan) and SECA Bodymeter 217 (SECA GmbH & Co., Hamburg, Germany), respectively. The measurements are recorded to the nearest 0.1 kg and 0.1 cm, respectively. The body mass index (BMI) of each child is calculated by dividing the measured weight (kg) by the square of the height (m). The World Health Organization (WHO) BMI-for-age growth reference for children aged 5–19 years old (30) served as the standard reference for determining the nutritional status of the children. The z-scores for BMI-for-age (BAZ) are determined using the software WHO AnthroPlus version 1.0.3, and children are classified into overweight (BAZ +1SD to +2SD) and obese (BAZ > +2SD) categories. The percentage of body fat is measured twice by bioelectrical impedance using the TANITA digital scale Model 300GS (Tanita Co., Tokyo, Japan) and nearest to 0.1 %. The children stood bare footed on the scale, after the electrode of the scale is cleaned to remove any debris. Any objects that could interfere with the readings are removed from their pockets before the measurements are taken.

Waist circumferences (WC) of the children are measured twice, according to the standardised protocol by the National Health and Nutrition Examination Survey (NHANES), which assessed the WC just above the right iliac crest at the mid-axillary line (Centers for Disease Control and Prevention National Health and Nutrition Examination Survey 2000). The WC is measured to the nearest 0.1 cm by using a Lufkin tape model W606PM (Apex Tool Group, Maryland, USA). Finally, the reported values of the body weight, height, percentage of body fat and WC are the average values from the two readings taken.

### Nutrient intake outcomes

The nutrient intakes are assessed using three non-consecutive days’ 24-h diet recalls, consisting of 2 weekdays and 1 weekend day over the period of a week, a method which had been used by many national surveys and studies on children (School Nutrition Dietary Assessment 2007). They are completed through face-to-face interviews with each children using household measurements, portion sizes and estimated weights of the food consumed. Tableware items such as bowls, dishes, spoons and glasses in commonly-used sizes, food models and pictures of common foods are used to assess the food intake to enhance the portion sizes and the estimation of their respective weights. Pictures from the book, *Atlas of Food Exchanges and Portion Sizes* (Suzana et al. 2009), is used to help the child estimate their food portion sizes. Additionally, energy, macronutrient, micronutrient and dietary fibre intakes are determined from the 3-day diet recalls using Nutritionist Pro™ software (Axxya Systems, United States), based principally on the Nutrient Composition of Malaysian Food (Tee et al. 2005) and the food product labels. The children’s nutrient intake is compared with the Recommended Nutrient Intakes for Malaysia (RNI) (National Coordinating Committee on Food and Nutrition (NCFFN) 2005).

